# Summary of the study

| Background/Rationale for the Research Plan | Oral mucositis occurs frequently when anticancer drugs and molecularly targeted drugs are administered, but prevention methods have not been established. In this study, we conducted a randomized controlled trial of the effect of betamethasone-containing drugs on preventing the onset of oral mucositis, using Aznol mouthwash as a control. |
| --- | --- |
| Target Diseases | Patients receiving drug therapy with solid tumors except head and neck cancers and blood cancers. |
| Primary Objective | The effect of betamethasone-containing drugs on preventing the development of oral mucositis will be examined. |
| Secondary Objectives | The effect of betamethasone-containing drugs on preventing the aggravation of oral mucositis will be examined. |
| Primary endpoint | The effect of betamethasone-containing drugs on preventing the onset of grade 1 oral mucositis will be compared with Aznol mouthwash as a control. |
| Secondary endpoints | The efficacy of betamethasone-containing drugs in preventing the development of grade 2 and grade 3 oral mucositis was compared with aznol mouthwash as a control. |
| Study design | Randomized controlled trials |

# At first

This study involves the off-label use of betamethasone and is categorized as a specified clinical trial under the Clinical Trials Act.

Thus, all parties involved in the study must adhere to the Clinical Trials Act during its implementation. The study will proceed after receiving approval from the Clinical Research Review Board and authorization from the administrators of the participating medical institutions.

[Clinical Research Review Committee]

| Name of the Committee | Nagasaki University Clinical Research Review Board  （The Clinical Research Review Board in Nagasaki University） |
| --- | --- |
| Installer | President, Nagasaki University |
| Certification Number | CRB7180001 |
| address | [name]  ([name]) |
| telephone number | [contact] |
| E-mail address | [[contact]](mailto:[contact]) |

# Research Background

Pharmacotherapy in cancer treatment has advanced dramatically with the introduction of molecular targeted therapies and immune checkpoint inhibitors, in addition to conventional cytotoxic anticancer agents. While pharmacotherapy has various adverse events, one significant adverse event is oral mucositis. Oral mucositis can cause severe pain, leading to the inability to consume food orally, which affects the nutritional status and may force the interruption of treatment for the primary disease, potentially affecting survival outcomes. However, there are no established treatments or preventive measures for oral mucositis associated with cancer therapy. The MASCC guidelines [1] suggest several measures, such as cryotherapy, oral care, analgesics, and zinc supplementation. However, there are no high-evidence preventive or therapeutic methods, and the current standard consists of symptomatic treatments like dietary modifications, local anesthetics, and opioid administrationThe efficacy and safety of steroid ointments for oral mucositis during head and neck radiation therapy were reported in the 1980s [2, 3], but it has not been widely adopted. One reason for this is the concern that local steroid application during radiation therapy or pharmacotherapy may promote the onset of oral candidiasis [4]. In response, we conducted a multicenter observational study showing that the risk factors for oral candidiasis during head and neck cancer radiation therapy were leukopenia and worsening mucositis. Our findings indicated that steroid ointment did not promote oral candidiasis but actually reduced its incidence, although the difference was not statistically significant [5]. However, steroid ointments are difficult to apply when mucositis extends to the pharyngeal mucosa, making steroid gargles easier to use. Unfortunately, no steroid gargles for mucositis are available in Japan.

In the BOLERO-2 trial, the incidence of oral mucositis during everolimus therapy for breast cancer was reported as 59%, with a higher incidence of 88.7% in a Japanese subgroup analysis [6]. A foreign trial demonstrated that dexamethasone gargles significantly reduced the incidence of Grade 2 or higher oral mucositis in everolimus-treated patients compared to a historical control group [7]. In Japan, where steroid gargles are not available, Umeda et al. showed in a phase III trial that the incidence of oral mucositis in patients treated with everolimus was reduced through dental interventions, including the application of dexamethasone ointment [8, 9]. Additionally, Hisahashi et al. showed that steroid gargles reduced the incidence of oral mucositis during pharmacotherapy for breast cancer [10]. There are also reports that local steroid gargle administration is effective and safe for treating oral mucositis induced by cytotoxic anticancer agents [11]. Given this background, we decided to evaluate the preventive effect of betamethasone gargle, a type of steroid, on oral mucositis in patients undergoing pharmacotherapy, through a randomized phase II trial.

# Purpose and Significance of Research

#### Purpose

The purpose of this study is to examine whether betamethasone gargles can prevent the onset or worsening of oral mucositis caused by pharmacotherapy.

#### Significance

This study aims to establish a preventive method for oral mucositis in patients undergoing pharmacotherapy, thereby contributing to improved quality of life (QOL) for these patients.

# Outline of Research

- 1. Methods of research

**Phase:** II

**Study Type:** Interventional Study

**Randomization:** Randomized Controlled Trial

**Blinding:** Open-label

**Control:** Azulene Gargle

**Allocation:** Parallel Group Comparison

**Study Objective:** Prevention

**Study Positioning:** Exploratory Study

- 1. Test Drug/Device

In this study, the following drugs were used as test drugs and control drugs.

The management of the test drug is described in "4.3 Management of the test drug / Management of the test device".

[Test drug]

| Generic name | Betamethasone sodium phosphate |
| --- | --- |
| Product Name /  Manufacturer / Distributor | Linolosal Injection 20mg (0.4%) (Wakamoto Pharmaceutical) |
| Dosage form, properties, and content | Sodium betamethasone phosphate in 1 ampoule 5 mL 26.3 mg (20 mg as betamethasone)  Clear, colorless aqueous injection |
| Medicinal classification | Synthetic corticosteroids |
| Indications | Anti-inflammatory effect, anti-allergy effect, immunosuppressive effect |
| Dosage | Injected or injected intravenously, intramuscularly, intraarticularly, intraspinal cavity, soft tissue, tendon sheath, nasal cavity, etc., or used in a nebulizer. As betamethasone,  〈Intravenous injection〉  Adults are usually injected intravenously at 2~8mg once every 3~6 hours.  〈Intravenous injection〉  Adults are usually injected 2~10mg 1~2 times a day.  〈Intramuscular injection〉  Normally, 2~8mg is injected every 3~6 hours for adults.  〈Intraluminal injection〉〈Intra-soft tissue injection〉〈Intra-tendon injection〉〈Intrasynovial fluid injection〉  〈Epidural injection〉  Adults are usually injected 2~10mg at a time. As a general rule, the interval between doses should be at least 2 weeks.  〈Intra-spinal injection〉〈Intrathoracic injection〉  Normally, 1~5mg per adult is injected 1~3 times a week.  〈Intralumen injection〉  Usually 0.4~1mg is injected once for adults.  〈Enema〉  Usually 0.4~6mg is injected once an adult.  〈Subconjunctival injection〉 Usually 0.4~2mg per adult injection. The amount of liquid at that time is 0.2 ~ 0.5 mL.  〈Postbulbar injection〉  Normally, 0.8~4mg is injected once for adults. The amount of liquid at that time shall be 0.5 ~ 1.0 mL.  〈Eye drops〉  Normally, 1~2 drops of 0.25~1mg/mL solution are instilled 3~8 times a day for adults.  〈Nebulizer〉  Usually, 0.1~2mg per adult is administered with a nebulizer 1~3 times a day.  〈Intranasal injection〉〈Paranasal injection〉  Adults usually inject 0.1~2mg 1~3 times a day.  〈Intranasal turbinate injection〉 Normally, 1~5mg is injected once per adult.  〈Nasal mushroom injection〉  Normally, 1~5mg is injected once per adult.  〈Laryngeal and tracheal injection〉〈Intra-middle ear cavity injection〉〈Eustachian tube injection〉  As betamethasone, it is usually injected 0.1~2mg once a day for adults 1~3 times a day.  〈Esophageal injection〉 Normally, 1~2mg is injected once per adult.  〈Injection into the salivary gland duct〉 Usually 0.5~1mg is injected once for adults. |
| Storage conditions | Store at room temperature (1~30°C) |

[Control drug]

| Generic name | Sodium azulene sulfonate hydrate |
| --- | --- |
| Product Name / Manufacturer /  Distributor | Aznol mouthwash 4% (Rothnitten Co., Ltd.), etc.* |
| Dosage form, properties, and  content | Dark blue liquid  Contains 40 mg of sodium azulene sulfonate hydrate in 1 mL |
| Medicinal  classification | Azulene-containing solution |
| Indications | Pharyngitis, tonsillitis, endostomatitis, acute flesh inflammation, glossitis, oral wounds |
| Dosage | As sodium azulene sulfonate hydrate, 4 to 6 mg (one press cut or 5 to 7 drops) is dissolved in an appropriate amount (about 100 mL) of water or slightly warm water, and soaking several times a day. In addition, it may be increased or decreased as appropriate depending on age and symptoms. |
| Storage conditions | Store at room temperature (1~30°C) |

* Other generic drugs (same ingredients, same dosage form) are also acceptable.

- 1. Subject/control drug management

The investigational drug used in this study will be purchased with research funds provided by the principal investigator and stored appropriately at each participating medical institution. The drug will be directly provided to participants for research purposes by the principal investigator, responsible investigator, or co-investigator. Any unused or expired drug due to missed doses will be disposed of according to the standard drug disposal procedures within the institution.

The control drug used in this study will be prescribed as part of routine clinical practice using standard prescriptions.

- 1. Selection Policy for Research Subjects

Eligible participants are those who meet all the inclusion criteria and none of the exclusion criteria as outlined below.

#### Inclusion Criteria:

- - 1. Patients undergoing pharmacotherapy for solid cancers, excluding head and neck cancers and hematological cancers, at participating facilities. The type or combination of anticancer agents, molecular targeted drugs, or immune checkpoint inhibitors does not matter.
    2. Patients aged 18 years or older at the time of consent.
    3. Patients who have received a thorough explanation of the study, fully understand its purpose and procedures, and have provided written informed consent voluntarily.

#### Rationale for Inclusion Criteria:

1. To ensure the study targets the intended population.
2. To include patients capable of making informed decisions.
3. To comply with the spirit of the Declaration of Helsinki.

#### Exclusion Criteria:

1. Patients with a history of hypersensitivity to betamethasone sodium phosphate.
2. Patients unable to perform gargling.
3. Patients with existing oral mucositis.
4. Patients diagnosed with oral candidiasis.
5. Patients deemed unsuitable for the study by the principal investigator, responsible investigator, or co-investigator.

#### Rationale for Exclusion Criteria:

1. To ensure the safety of study participants.
2. To include only those for whom the study can be conducted.
3. Since this study focuses on the preventive effects of the drug, patients with existing oral mucositis are excluded.
4. To avoid the potential risk of exacerbating oral candidiasis through the use of steroid gargles.

To ensure both participant safety and proper study implementation by allowing investigators to exclude unsuitable candidates.

- 1. Overview of treatment (protocol treatment)

Patients undergoing pharmacotherapy for solid cancers, excluding hematological cancers and head and neck cancers, will be divided into two groups for evaluation. After obtaining consent and completing registration, participants will be randomly assigned to either the betamethasone gargle group or the azulene gargle group. The evaluation will include the items specified in section 4.10.

No oral mucositis

No development of oral candidiasis

Betamethasone

8 weeks follow-up

Allocarion

Registratiton

Aznol containment

8 weeks follow-up

After confirming that eligible patients meet the inclusion criteria and do not have oral mucositis or oral candidiasis, they will be registered and randomly assigned to either the intervention group or the control group in a 1:1 ratio.

Intervention Group: In addition to standard oral care*, patients will gargle with 10 ml of 0.01% betamethasone solution four times daily (after each meal** and before bedtime), swishing it in their mouths for 30 seconds to 1 minute.

Control Group: In addition to standard oral care*, patients will gargle with 10 ml of 4% azulene solution four times daily (after each meal** and before bedtime), swishing it in their mouths for 30 seconds to 1 minute.

The use of steroid ointments on the oral mucosa is prohibited for both groups.

Note: For patients who do not eat meals, the gargle should be performed at meal-equivalent times. Standard Oral Care:

Includes modifications to dietary consistency, administration of analgesics or opioids, oral hygiene measures, and use of moisturizers.

Method for Diagnosing Oral Candidiasis:

Oral candidiasis is diagnosed if symptoms suggestive of candidiasis are identified by the attending cancer physician or oral care specialist, irrespective of whether a culture test is performed or its results.

- 1. Criteria for treatment (protocol treatment)

If oral candidiasis occurs during the treatment, gargling will be suspended in the betamethasone group and resumed once the candidiasis resolves. In the azulene group, gargling will continue even if oral candidiasis is detected.

- 1. Concomitant treatment

No specific concurrent drugs or therapies are mandatory for this study.

- 1. Prohibited Drugs / Devices / Therapies

The use of steroid ointments on the oral mucosa is prohibited during the study period.

- 1. Combined use of limiting shalf/combined use of limiting machine/combined use of limiting therapy

There are no restricted drugs or therapies defined for this study.

- 1. Assessments, collection items and schedules
- Schedule (Table)

|  | Regustration/assignment | Medical examination | | | | At exit | At the time of cancellation |
| --- | --- | --- | --- | --- | --- | --- | --- |
|  |  | 1~2 weeks | | | | Week 8 ends |  |
| Obtaining  consent | ● | － | － | － | － | － | － |
| Allocation | ● | － | － | － | － | － | － |
| Information gathering 1 | ● | － | － | － | － | － | － |
| Information gathering 2 | － | ● | ● | ● | ● | － | － |
| Information gathering 3 | － | － | － | － | － | ● | ● |

*1 The date of registration can be before or after the start of chemotherapy. The date of registration and the date of allocation can be different days.

*2 Once a week for inpatient treatment or at the time of hospitalization, and on the day of treatment for outpatient treatment

In the case of postponement of cool, inclusion and information gathering will be carried out according to the postponement

Dental examinations are not mandatory, and dentists are allowed to visit outpatient chemotherapy rooms for examinations

- Observation and Inspection Items

[Items to be collected at the time of registration]

| Item | Detail |
| --- | --- |
| Patient  Background | Age, sex, anamnesis and medication administered, primary site, smoking  history, alcohol consumption history, weight |
| Treatment-  related factors | The day of the start of treatment, the name of the anti-cancer drug, and the  use of drug/ combined therapy |
| Clinical laboratory findings (In-hospital  examination) | Neutrophil count, lymphocyte count, albumin, creatinine |
| Oral findings | Presence and grade of oral mucositis (CTCAE v3.0 and v5.0), number of remaining teeth, presence or absence of dentures, periodontal examination values (periodontal pockets, bleeding, upset), degree of plaque adhesion (OHI-S), degree of denture cleaning (in the case of dentures), presence and location of untreated teeth, degree of alveolar bone resorption in patients with dental X-rays |

[Information to be collected at the time of visit after allocation]

| Item | Detail |
| --- | --- |
| Oral mucositis | Presence and grade of oral mucositis (CTCAE v3.0 and v5.0), and date of onset in cases |
| Candida onset | Presence and timing of onset |
| Drugs for research use | Usage  Presence or absence of adverse events related to the study drug (inflammatory changes such as redness and swelling of the oral mucosa) |
| Adverse events | Presence or absence of the development of taste disorders, oral infections and other adverse events |

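### The control regimen gives azulene's bottled strength (4%) as the rinse strength, while the protocol's own drug table dilutes that product to about 0.004–0.006%

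*Protocol*

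**What the plan says.** The Protocol describes the control rinse in two places.

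- **Overview of treatment (protocol treatment), Control Group.** This is the trial regimen: "patients will gargle with 10 ml of 4% azulene solution four times daily", after meals and before bedtime. It mentions no dilution.
- **Outline of Research, control drug table.** The product is a liquid sold as a 4% mouthwash; its content row reads "Contains 40 mg of sodium azulene sulfonate hydrate in 1 mL". Under Dosage, "4 to 6 mg (one press cut or 5 to 7 drops) is dissolved in an appropriate amount (about 100 mL) of water". The table also lets the dose be adjusted for age and symptoms. It does not say how much of the prepared liquid is used at each gargle.

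Three other statements bear on how to read these:

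- The parallel Intervention Group sentence says "patients will gargle with 10 ml of 0.01% betamethasone solution four times daily".
- The section on managing the study drugs says "The control drug used in this study will be prescribed as part of routine clinical practice using standard prescriptions".
- The opening section (At first) states "This study involves the off-label use of betamethasone" and names no other drug as off-label.

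**The concern.** The treatment section tells a site what the comparator is. Followed literally, it has control patients rinse with undiluted concentrate, which conflicts with the product's directions as the Protocol reproduces them. The test-arm sentence has the same form (a volume of a solution at a stated percentage), and its percentage is the strength in the mouth after dilution from a stronger ampoule. A reader therefore has reason to take the 4% the same way.

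What is at stake is the definition of the comparator. The section on compliance with the research protocol does not let investigators depart from or change the Protocol without prior approval. A site should not have to decide which of two conflicting descriptions to follow. A reader of the public Protocol could also take away the wrong comparator strength.

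**Working it through.** **Inputs, all from the Protocol**

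- Control product: 40 mg/mL (control drug table).
- Directed preparation: 4 to 6 mg in about 100 mL of water (same table, Dosage).
- Control rinse as instructed: 10 mL at 4%, four times daily (Overview of treatment), with 8 weeks of follow-up.
- Test product: 20 mg betamethasone in a 5 mL ampoule (test drug table), rinse at 0.01% (Overview of treatment).

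**Formula:** % w/v = (mg/mL) / 10.

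**Step 1. Reproduce the stated figure.** 40 / 10 = 4%. The 4% in the Control Group sentence equals the bottled strength.

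**Step 2. Strength after the directed dilution.**

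- 4 mg / 100 mL = 0.04 mg/mL = 0.004%
- 6 mg / 100 mL = 0.06 mg/mL = 0.006%

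**Step 3. Size of the conflict.** 4 / 0.006 = 667 and 4 / 0.004 = 1,000, so 667- to 1,000-fold.

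**Step 4. Can a smaller water volume close the gap?** The table leaves the volume partly to judgement. As an extreme assumption, dissolve the whole dose in only the 10 mL gargled:

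- 4 / 10 = 0.4 mg/mL = 0.04%, and 4 / 0.04 = 100
- 6 / 10 = 0.6 mg/mL = 0.06%, and 4 / 0.06 = 67

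A 67- to 100-fold gap remains.

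**Step 5. What literal use would mean.**

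| Quantity | As written | Per the drug table |
| --- | --- | --- |
| Azulene per use | 10 × 40 = 400 mg | 4–6 mg prepared |
| Product per use | 10 mL | 4/40 = 0.10 mL to 6/40 = 0.15 mL |
| Product over 8 weeks (4 × 56 = 224 uses) | 2,240 mL | 22.4–33.6 mL |

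One literal rinse would consume the product for 10 / 0.15 = 67 to 10 / 0.10 = 100 directed preparations. That is implausible under ordinary prescribing and points to a slip in the text.

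**Step 6. The parallel sentence.** The ampoule is 20 / 5 = 4 mg/mL = 0.4%, and 0.4 / 0.01 = 40. The test-arm percentage is thus the strength after a 40-fold dilution, whereas the control-arm percentage is the strength before dilution.

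**Step 7. What the 10 mL means once the dilution is restored.** Ten mL of the 100 mL preparation holds 0.4–0.6 mg; the full preparation holds 4–6 mg. The documents do not settle which is intended, and the two differ 10-fold in azulene per gargle.

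**The case against.** The best defence is that the 4% is a product identifier that also covers generics of the same strength, and that the Protocol supplies the preparation elsewhere. The control drug table gives the dilution, and routine prescribing tells a site to follow it. On this view the asymmetry between the two arms has an ordinary cause. The betamethasone product is an injection whose dosage row contains no gargle regimen, so the treatment section had to state the final strength. Azulene already had gargle directions. A site that dilutes according to the table is also following the Protocol, so it is not clearly deviating.

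Much of this stands. It makes labelled dilution the likely practice and limits the seriousness of the point. It does not make the sentence correct. The sentence specifies a volume of solution at a percentage, and nothing in it refers to the table. Nor does the table declare its dosage rows to be the trial regimen; the betamethasone row lists injection, eye-drop and nebulizer doses that plainly are not.

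A reader might infer something stronger: that control patients actually rinse with concentrate, so that the comparator is distorted and the treatment comparison compromised. The documents do not support this. No statement says that undiluted use is intended, only betamethasone is called off-label, and the quantities in Step 5 make literal use implausible. The 667- to 1,000-fold figure measures a conflict in the text; it does not estimate exposure.

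**Conclusion.** The point holds as an internal contradiction in the control regimen. The bottled strength of 4% stands where the rinse strength should be, against a nominal 0.004–0.006% in the Protocol's own table. The nominal range assumes the stated dose and about 100 mL of water. The conclusion does not depend on the exact volume, because the gap is still at least 67-fold when the whole 4 to 6 mg is dissolved in 10 mL.

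It is most likely a wording error. No effect on the primary comparison, the analysis sets or the target of 296 participants follows from it. It ranks as minor to should-fix: the likely practical consequence is small, but the wrong figure sits in the instruction that defines the comparator.

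**What to change.** In the Control Group sentence, replace the 10 mL of 4% solution with the 4% product diluted as in the control drug table: 4 to 6 mg of sodium azulene sulfonate hydrate (one press or 5 to 7 drops) in about 100 mL of water. Keep the frequency and the swishing time.

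Before the wording is final, the sponsor should confirm whether each gargle uses 10 mL of that dilution or the full preparation. The 10 mL may simply mirror the betamethasone sentence, and fixing it without asking could set a weaker comparator than routine use. Then send sites a short clarification.

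The cost is one amended sentence, taken through the review board as a Protocol change, one question to the sponsor and one notice to sites. Sample size, data collection and analysis stay as they are.
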